### Algorithm 1.0

is a mathematical instrument that determines the required nursing home staff (in number and qualification) based on the number of residents and their care mix within a nursing home. The mean actual and targeted numbers of care interventions and time of provided care (per care dependent in a certain period) can be combined multiplicatively, and required staff numbers can be derived. The primary outcome of applying the algorithm is that for Germany, about 36% more nursing home staff are required to provide adequate needs-oriented care. The input for this calculation was the care mix of all nursing home residents in Germany. The plus of 36% full-time equivalents refers to a care-degree standardized reference nursing home with 100 residents [15]. However, the instrument addresses the overall number of required nursing home staff and specifies it according to the different QL described above. It was found that the lack of staff varies according to the QL of nursing home staff. In the legally given three qualification groups described above, the additional demand for staff in unqualified and semi-qualified nurses was 69,0%. In contrast, for qualified nurses with higher QLs, it was only 3.5% [15].

Based on the study results, the German legislature commissioned a model program to (i) trial and evaluate both measures (increased staffing and work organization), (ii) derive a concept for a national rollout, and (iii) use the findings from the evaluation to parameterize *Algorithm 2.0.* The contracting authority of this model program is the GKV-Spitzenverband (*Spitzenverband Bund der Krankenkassen* – National Association of Statutory Health Insurance Funds).

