Ten matched nursing homes as a control group do not undergo the two intervention measures but participate in the evaluation. Matching criteria are the federal state, number of beds, and ownership. The evaluation assesses (a) the quality of care, (b) the job satisfaction, and (c) the effects on the actual-target differences in number, duration, and QL fit of care provision as defined in step 3 (summative evaluation). QL-fit means that the required QL of the intervention (determined by the complexity of the intervention in interaction with the level of stability of the care situation of the nursing home resident) fits the QL of the nurse. Effects of the intervention concerning (a) and (b) will be measured using a difference-in-difference approach in the intervention and control group nursing home facilities. The difference in difference analysis can be applied when evaluating outcomes associated with healthcare policy implementation. This analysis's beneficial characteristic is the possibility of controlling for background changes [19]. The evaluation compares the pre- and post-intervention differences in outcomes in (a) and (b)—as operationalized below—between the treatment group (10 nursing homes retrieving the intervention) and the control group (10 nursing homes not retrieving the intervention). Endpoint (c) will only be investigated through a pre-post comparison with the intervention group, as the shadowing of the control group was regarded as too resource-intensive.

The study will involve 20 nursing homes in Germany (10 in the intervention group and 10 in the control group), nursing home staff, residents, about 120–150 data collectors (so-called ‘nurse shadowers’), and about 20 assessors and evaluators on behalf of the LTC insurance funds (Medizinische Dienste/medicproof GmbH). The respective work packages describe the participants' involvement in detail.

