## Eligibility criteria

Several targeted groups are involved in the study. Nursing home staff must fulfill partially varying inclusion criteria for participation in the different activities. For the survey, they must be involved in the care of the respective nursing home residents and working in the home before the start of the survey. For the shadowing, they must work in the shadowed living area (only in the intervention group). The focus groups must be employed in a participating nursing home from the beginning of the intervention (only in the intervention group). For the competency analysis, they must work in one of the nursing facilities of the intervention group.

Nursing home residents may participate in the survey if they can complete the questionnaire alone or with assistance. A proxy rating will be applied for nursing home residents with cognitive impairments. Participation in the shadowing is possible for nursing home residents if they live in the respective shadowed living area. Terminal residents and residents living in the respective nursing home for less than four weeks will be excluded from the shadowing and the survey.

The inclusion criteria for the shadowers participating in data acquisition (i.e., shadowing) are registration as a qualified (geriatric) nurse and participation in training provided by the study team. There are no further inclusion criteria for the shadowers' survey.

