## Summative evaluation

The customized concepts will be practiced, refined, and evaluated in the third study phase. The evaluation is planned as a prospective interventional study. In the intervention group, all elements of the data acquisition for the summative evaluation will take place as pre-post-comparison at two points in time (t_0_ before the intervention and t_1_ after the implementation of the changes in organization and staffing) at an interval of one year (note that the shadowing only takes place in one living area per care home). To control for general trends in the dynamic LTC setting and the effects of the revision of Paragraph 113 Section C of the German Social Code, Part 11 (that enacted a new finance of staffing ratios based on *Algorithm*
1.0) 10 nursing homes from the intervention group are matched with ten nursing homes in the control group by state, number of beds, and ownership. The control group undergoes the surveys of the summative evaluation but not the shadowing nor the two intervention measures. A (cluster) randomization was not possible due to the stipulations of the statutory order.

The summative evaluation assesses the effects of the intervention on (i) quality of care, (ii) job satisfaction, and (iii) changes in the difference between (a) the number of provided interventions, (b) the duration of the provided interventions, and (c) the extent of qualification-fitting. Table 2 provides an overview of the data collection methods for the endpoints of the summative evaluation.

**Table 2 Tab2:** Data collection methods for the endpoints of the summative evaluation

Methods and instruments	Operationalization of the endpoints

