## Statistical analysis

No data will be collected during the development of an initial implementation concept, and no statistical analysis will be conducted. In the second work package, the actual status of the nursing homes, e.g., the infrastructure, the resident structure, the organization of the nursing homes, technical equipment, and the competencies of the staff, will be depicted. Information regarding the actual status will be analyzed descriptively.

The summative evaluation first analyzes the results of the mandatory external quality assessments descriptively. The analysis examines the development of the quality of care over the intervention period (t_0_, t_1_) in a pre-post comparison, both for the pertinent nursing homes and the control group, and the differences in the trends between them (difference-in-difference approach). Secondly, a descriptive analysis of the surveys on nursing home residents will be carried out. The analysis of the job satisfaction survey is carried out for the two subscales of the EXQ according to the method specified in the instrument. The subscales of the StressBarometer are not analyzed according to the specified scoring for workload but only in a descriptive comparison of the aggregated subscales and the individual items between the intervention and the control group and, in particular, for the indirect measurement of change in the intervention group (pre-post comparison). The analysis will examine changes in job satisfaction in t_1_ compared to t_0_ and if these changes differ between the intervention and control groups. Stratified evaluations are planned according to occupational groups and QLs. The answers to the questions on direct change measurement (t_1_ survey) will be analyzed quantitatively as far as possible; qualitative data will be summarized narratively if necessary. From the shadowing data of the intervention group, rates of the number and duration of the (non-)performance of the planned and the performed interventions are calculated (actual and targeted quantitative aspects of care). Furthermore, the change between t_0_ and t_1_ will be shown. Moreover, the analysis will examine the extent of qualification-oriented work organization and the change between t_0_ and t_1_ (actual and targeted qualitative aspects of care). The survey of the shadowers will be evaluated descriptively concerning the quality of care, possible causes of any deficits observed, and perceived changes due to the intervention.

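### The uncontrolled t0–t1 shadowing comparison is made on whichever residents are present at each wave, so the stated change cannot be separated from a change in resident mix and should not be called an effect

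*Protocol article*

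**What the plan says.** The protocol article (Study design and participants) states: "Endpoint (c) will only be investigated through a pre-post comparison with the intervention group". The reason given is that shadowing the control homes would take too many resources.

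The Summative evaluation section places the two waves "at an interval of one year" and notes that "the shadowing only takes place in one living area per care home". Under Eligibility criteria, "Participation in the shadowing is possible for nursing home residents if they live in the respective shadowed living area", and "Terminal residents and residents living in the respective nursing home for less than four weeks will be excluded from the shadowing and the survey". No rule requires a resident to be present at both waves.

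For the shadowing data, the Statistical analysis section says that rates of performance and non-performance are calculated for number and duration, and then: "Furthermore, the change between t_0_ and t_1_ will be shown". The extent of qualification-oriented work organisation and its change are to be examined in the same way.

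The interpretation is causal. Summative evaluation says: "The summative evaluation assesses the effects of the intervention on (i) quality of care, (ii) job satisfaction, and (iii) changes in the difference". The background section on the PeBeM data collection method adds that a smaller gap between actual and target values may be read as better quality of care. The Limitations section qualifies the shadowing only on transferability beyond one living area and does not mention resident turnover.

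**The concern.** Over a year some residents die or move out and have no t1 value. Others arrive and have no t0 value. Those who stay are a year older. The two waves therefore describe overlapping but different groups.

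The article itself ties care requirements to the resident. The legal background section derives mean required time from the care grade. Study design and participants makes the required qualification level depend partly on how stable the resident's care situation is. The Algorithm 1.0 section reports its main result on a standardised basis: "The plus of 36% full-time equivalents refers to a care-degree standardized reference nursing home with 100 residents".

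The control homes were added to absorb general trends, but they are not shadowed, so nothing in the stated comparison distinguishes a shift in resident mix from a change in practice. These are the only direct data on number, duration and qualification fit, and they also feed the refinement of the algorithm.

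**Working it through.** The article gives no turnover rate, care-grade mix, number of shadowed residents or omission rate by grade, so there is no plan figure to reproduce. The checks below ask how far each scale moves when practice within each level of need is held fixed. **All numerical inputs are assumptions.**

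**1. Which indicators can move?** Table 3 takes the target number from the individual daily plan and the shadowers' assessment, the target duration from the shadowers' assessment, and the target qualification level from the needs assessment and daily plan. Targets therefore follow the residents present.
- Actual/target rates and qualification fit move with the mix only if fulfilment or fit differs by need.
- Table 2 also lists actual and targeted number and duration as separate indicators, and endpoint (c) is named a difference. On an absolute scale these move with need even when fulfilment is equal.

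**2. Care-grade illustration.** Assumed for grades 2/3/4/5: shares p = 20/35/30/15%; relative need w = 1.0/1.3/1.6/1.9; omission o = 15/20/25/30%. Mean need = Σp·w, mean gap = Σp·w·o, omission rate = gap ÷ need.

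At t0:
- need = 0.200 + 0.455 + 0.480 + 0.285 = 1.420
- gap = 0.0300 + 0.0910 + 0.1200 + 0.0855 = 0.3265
- rate = 0.3265 ÷ 1.420 = 23.0%

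Now move 7.5% or 15% of residents from grades 2–3 to grades 4–5, in proportion to the existing shares (20:35 out, 30:15 in). Shares become 17.3/30.2/35.0/17.5% or 14.5/25.5/40.0/20.0%.

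| Shift | Need | Gap | Change in gap | Omission rate | Change in rate |
|---|---|---|---|---|---|
| none | 1.4200 | 0.3265 | – | 23.0% | – |
| 7.5% | 1.4582 | 0.3443 | +5.4% | 23.6% | +0.6 points |
| 15% | 1.4964 | 0.3620 | +10.9% | 24.2% | +1.2 points |

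With omission flat at 23% in every grade, the gap is 0.23 × need: 0.3266, 0.3354 and 0.3442, or +2.7% and +5.4%. The rate stays at 23.0%.

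**3. Two-level illustration in the other direction.** Assumed: target 80 or 140 minutes per resident-day for lower or higher need; half the residents higher-need at t0; 20–40% replaced; higher-need share 20–30 points lower among newcomers than leavers. One case, with 30% replaced and a 20-point difference: the higher-need share falls from 0.50 to 0.50 − 0.30 × 0.20 = 0.44, and the mean target from 110.0 to 106.4 minutes.
- Fulfilment 75% in both groups: actual 82.5 to 79.8, gap 27.5 to 26.6 (−3.3%), ratio unchanged at 0.75.
- Fulfilment 80% and 70%: actual 81.0 to 79.0, gap 29.00 to 27.44 (−5.4%), ratio 0.7364 to 0.7421 (+0.57 points).

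Over the whole grid, equal fulfilment gives 0.00 points on the ratio and on qualification fit, and −2.2% to −6.5% on raw actual minutes and on the absolute gap. With fulfilment and fit 5–20 points lower in higher-need residents, the ratio and fit rise by 0.2 to 2.4 points and the gap shrinks by 2.9% to 14.6%. If newcomers have higher needs than leavers, the direction reverses.

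**4. Purely random turnover.** With the inputs of step 2, ten areas of 25 residents and 20–35% replaced by residents drawn from the same mix, the SD of the relative change in the gap is about 1.7–2.2% pooled and 5–7% in one area. For the omission rate it is about 0.20–0.26 points pooled and 0.6–0.8 in one area.

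**5. Effect of standardising.** Weighting the t1 within-grade values by the t0 shares returns the t0 figures in steps 2 and 3. The spurious change is then exactly 0, because practice within each level was held constant.

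**The case against.** The strongest reply is that the design already handles care mix. A new needs assessment and an individual daily plan are part of the method, and all elements are repeated at both waves, so a resident with greater needs brings a higher target. This stands for the rates, which are what the Statistical analysis section says are calculated: they move only if fulfilment varies with need, and the documents give no evidence on that either way. A reader might infer that any mix shift passes straight into endpoint (c) and is reported as better or worse care. The documents do not support that. They also do not say that the mix will shift.

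Second, this is a condensed article, and an adjustment may be specified in a full analysis plan. That stands as well: silence on adjustment is not the defect, and the wording does not exclude standardisation. What the article does state is an uncontrolled comparison of an open population, described as an effect.

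Third, the magnitude depends on invented inputs. If two thirds of the shift left grade 2 and two thirds entered grade 5, the gap would rise by 7.5% and 15% instead of 5.4% and 10.9%. The larger case would halve grade 2 and take grade 5 from 15% to 25% within a year, for which there is no support. Random turnover alone is negligible for the pooled rate.

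Fourth, the Algorithm 1.0 figure was standardised for a different purpose, a national staffing estimate. It shows that the investigators regard care grade as relevant, not that they have contradicted themselves.

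**Conclusion.** The concern holds in limited form. The stated t0–t1 change in endpoint (c) is uncontrolled and rests on whichever residents are present at each wave, so the article's description of it as an effect of the intervention is not supported by the stated comparison.

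- Exposed without further conditions: raw number and duration, and any absolute actual-target difference.
- Exposed only if fulfilment or fit differs by need: actual/target rates and qualification fit.

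On the assumed inputs with a proportional 7.5–15% shift to higher grades, the absolute gap changes by about 5–11% and the omission rate by about 0.6–1.2 points. With equal fulfilment the rate change is zero. Actual size and direction cannot be derived from the documents. The remedy is worth making because it uses data that the method already collects.

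**What to change.** Using the needs assessment that forms part of the data collection at each wave:

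- Report the care-grade mix at t0 and t1 and the number of residents shadowed at both.
- Present the endpoint (c) change standardised directly to the pooled t0 care-grade distribution, beside the crude change. Standardise over the ten areas pooled, or in two care-grade bands, because strata within one living area will be small.
- Add a comparison in residents shadowed at both waves, as a sensitivity analysis only. It selects survivors and does not remove a year's ageing.
- Describe the result as a change in the intervention homes, not as an effect of the intervention, and name resident turnover under Limitations.

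The cost is a little more analysis and some loss of precision from small strata; no new data are needed. Standardisation leaves differences in need within a grade, and it does not replace the missing control group, so the wording change is needed in any case.

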## Discussion

In Germany, in July 2023, a revision of Paragraph 113 Section C of the German Social Code, Part 11, was enacted to reform the refinancing of staffing in LTC. The calculation of staffing ratios applied in this paragraph is based on *Algorithm*
1.0, which resulted from the PeBeM1 study. During the ongoing dynamic process of legislation regarding the further development of the LTC sector, the PeBeM3 study now investigates a combination of staffing calculation and work organization to generate an evidence-based strategy for elaborating the care system. Socio-cultural and economic challenges in the organization and provision of LTC affect most of Europe. Thus, developing new work organization and resource distribution strategies is relevant for further developing healthcare systems. Furthermore, a qualification-oriented work organization has yet to be developed and evaluated in the given setting. It could be transferred to and implemented in other healthcare systems. Therefore, the study's results will be considerable for nursing sciences – not just in Germany. For experts in different countries, the study will hopefully serve as a template to restructure LTC financing or work organization.

## Limitations

As the duration of the intervention is short for the immense changes in the organizational structure and processes, the positive effect of the intervention may be underestimated. Furthermore, the restricted budget allowed us to select only ten facilities in the intervention group. This implies that we could only involve some German states. As the final selection resides by the funder, selection bias could occur. In those ten facilities, the shadowing will be performed only in one of the living areas, so the transferability of the results to the whole facility may be restricted. The transferability of the customized concepts is limited as the number of participating nursing homes is restricted to ten. However, the prototypical concepts developed for the national rollout are open for individual adaptation and thus can be applied in every German nursing home.

## Data Availability

The resulting datasets will be available exclusively for scientific purposes from the principal and funding body GKV-Spitzenverband (Spitzenverband Bund der Krankenkassen—National Association of Statutory Health Insurance Funds) upon reasonable request.

## Abbreviations

DIP: Daily intervention planning (*tagesstrukturierte Interventionsplanung*)
EXQ: Employee Experience Questionnaire
GKV-SV: GKV-Spitzenverband (*Spitzenverband Bund der Krankenkassen*-National Association of Statutory Health Insurance Funds)
LTC: Long-term care
PeBeM: Acronym for the German word *Personalbemessung*, referring to the PeBeM1 study ‘Development of a scientifically based procedure for the standardized calculation of staffing requirements in long term-care’ and the PeBeM3, which is the subject of the study protocol presented here
QL: Qualification Level (*Qualifikationsniveau*)
QMM: Qualification mis model (*Qualifikations-Mix-Modell*)
